
### Treatments

2.3

Cobimetinib (provided by Hoffmann-La Roche) is an oral selective inhibitor of the MEK pathway. Vemurafenib (provided by Hoffmann-La Roche) is a low-molecular-weight inhibitor of BRAF serine–threonine kinase. Atezolizumab (provided by Hoffmann-La Roche) is an anti-PD-L1 antibody.

The study will include three possible treatments: (1) vemurafenib 960 mg twice daily per os from day 1 to 42; (2) vemurafenib 720 mg twice daily per os from day 1 to 42; (3) cobimetinib 60 mg once daily per os from day 1 to 21 and from day 29 to 42; cobimetinib should not be taken on days 22–28; and (4) atezolizumab 840 mg intravenous for two cycles (days 22 and 43).

Patients will be randomized to three different arms: A) *BRAF*-mutated patients will receive (1) + (3) for 6 weeks; B) *BRAF*-mutated patients will receive (2) + (3) + (4) for 6 weeks; C) *BRAF* WT patients will receive (3) + (4) for 6 weeks.

All patients will also receive atezolizumab 1200 mg intravenous every 3 weeks for 17 cycles after surgery and after a second screening period (up to 6 weeks).

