Some biomarkers and parameters proposed as potential predictive biomarkers for immunotherapy (i.e., C-reactive protein; LDH; absolute neutrophil, monocyte, eosinophil, and lymphocyte counts) will be correlated with pathological response and patient outcome.

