### Data analysis

2.6

All enrolled patients receiving at least one dose of the study medication will be considered the intention-to-treat population (ITT). The patient subgroup of the ITT population receiving at least one dose of the study drug will define the safety population. The analysis of efficacy endpoints will be performed in the ITT population, whereas the safety analysis will be performed in the safety population. A primary data analysis assessing the primary endpoint will be available after the neoadjuvant phase. A final data analysis will be available at study closure. The safety analysis will be completed within 12 months from the last visit of the last patient.

Primary endpoint results will be reported as counts and rates with confidence intervals. No comparisons among arms are planned. Demographical and clinical characteristics will be presented as descriptive statistics and summarized according to the treatment arm. Categorical variables will be given as counts and percentages, quantitative ones as mean and standard deviation, or median and interquartile range, as appropriate. No adjustment for multiple testing will be made.

Safety and tolerability will be assessed regarding AEs, laboratory data, ECG data, vital signs, and weight, which will be collected for all patients. AEs [both in terms of MedDRA preferred terms (26) and CTCAE 5.0 grade (27)], laboratory data, ECG data, vital signs data, and weight will be listed individually by the patient and summarized. Prevalence of related AEs, by grade, will be presented with a 95% CI. Survival will be represented with Kaplan-Meier curves, from which the median with 95% CIs will be derived.

Due to the small sample size, statistical analysis of biomarkers data will be conducted with the aim of hypothesis generation. A complete description of the data will be done. For biomarkers that might change over time due to treatment, levels before and after treatment will be compared with appropriate statistical tests based on the data type. Correlation with outcomes will be evaluated with univariate regression models. p ≤ 0.05 will be considered significant, and no adjustment is planned for multiple comparisons due to the exploratory nature of the analysis.

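### The biomarker–outcome models have no arm or BRAF term and are not stated to be within arm; if pooled, markers that track BRAF status are more likely to look associated with pCR

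*Protocol article*

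**What the plan says.** Section 2.6 (Data analysis) of the protocol article fixes the method: "Correlation with outcomes will be evaluated with univariate regression models". It sets the criterion in the next sentence: "p ≤ 0.05 will be considered significant, and no adjustment is planned for multiple comparisons due to the exploratory nature of the analysis". It also gives the purpose: "statistical analysis of biomarkers data will be conducted with the aim of hypothesis generation". Section 2.4 (Endpoints and assessments) adds that several candidate markers for immunotherapy, such as LDH and blood counts, "will be correlated with pathological response and patient outcome".

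Section 2.6 does not say whether these models use all patients together or one arm at a time. For the main results it says "No comparisons among arms are planned", and it plans to summarise baseline characteristics by treatment arm. It makes no such statement for the biomarker models.

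Section 2.3 (Treatments) shows how the arms differ, where (1) and (2) are vemurafenib regimens, (3) is cobimetinib and (4) is atezolizumab:

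- Arm A: BRAF-"mutated patients will receive (1) + (3) for 6 weeks"
- Arm B: BRAF-"mutated patients will receive (2) + (3) + (4) for 6 weeks"
- Arm C: BRAF "WT patients will receive (3) + (4) for 6 weeks"

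Section 2.5 (Sample size) assumes a pCR rate of 60% in arms A and B (27 patients each). For arm C (34 patients) it gives about 30% in one sentence and 35% in the power sentence.

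**The concern.** A univariate regression has one predictor, the marker. In a pooled fit, nothing then separates the effect of the marker from the effect of belonging to a BRAF group. By the plan's own assumptions that group is strongly related to pCR. Any marker whose level differs between BRAF-mutated and wild-type patients therefore picks up an association with pCR, even if it says nothing about response among patients of the same BRAF status.

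The introduction of the article gives a reason to expect some such differences, at least after treatment starts. It reports that MEK and BRAF inhibition raises PD-L1 expression and T-cell infiltration. Both PD-L1 and Immunoscore are on the marker list, and the arms receive different drugs.

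At stake is the quality of the hypotheses that the trial hands on. A marker that only stands in for BRAF status adds nothing, because BRAF status must be known at entry.

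**Working it through.** **Inputs**

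- From section 2.5: 27 + 27 = 54 BRAF-mutated patients with pCR 60%, and 34 wild-type patients with pCR 30% or 35%. 54 + 34 = 88, the total in section 2.2.
- From section 2.6: p ≤ 0.05, taken as two-sided (an assumption, since sidedness is not stated).
- Assumed: a normally distributed marker whose mean differs by d SD between BRAF groups and which is unrelated to pCR within each group. The documents give no value for d, so a range is shown.

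**The plan's own figures.** Exact binomial power for n = 27, 30% against 60%, is 92.6% with a cut-off of 13 responders (one-sided alpha 3.6%), in line with the stated minimum of 90%. For n = 34, 15% against 35%, a cut-off of 10 gives 80.4% (alpha 2.4%), in line with the stated 80%. The assumed pCR rates are therefore those on which the sample sizes rest. The cut-off of 12 printed for arms A and B is a separate matter and does not enter here.

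**How the association arises.** With arm C at 30%, the expected number of responders is 54 × 0.60 + 34 × 0.30 = 32.4 + 10.2 = 42.6, and of non-responders 21.6 + 23.8 = 45.4. The share of BRAF-mutated patients is 32.4/42.6 = 0.761 among responders and 21.6/45.4 = 0.476 among non-responders. The marker mean therefore differs by (0.761 − 0.476) × d = 0.285d between responders and non-responders, with no within-group link at all.

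Hand check at d = 1:

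- The marker variance is 1 + 0.761 × 0.239 = 1.182 in responders and 1 + 0.476 × 0.524 = 1.249 in non-responders.
- SE = √(1.182/42.6 + 1.249/45.4) = 0.235, so z = 0.285/0.235 = 1.21.
- The chance of p ≤ 0.05 is about Φ(1.21 − 1.96) = Φ(−0.75) = 23%.

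**Simulation.** 4,000 trials per setting, logistic model for pCR, share of trials with p ≤ 0.05:

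| Shift d (SD) | Pooled univariate, arm C 30%: Wald / score test | Pooled univariate, arm C 35%: Wald / score test | With BRAF term (Wald), arm C 30% / 35% |
|---|---|---|---|
| 0 | 5.0% / – | 4.8% / – | 5.0% / 4.8% |
| 0.5 | 8.9% / 10% | 8.5% / 8% | 4.6% / 5.3% |
| 1.0 | 21.0% / 23% | 16.0% / 17% | 4.2% / 4.7% |
| 1.5 | 37.0% / 37% | 26.6% / 28% | 4.8% / 5.2% |
| 2.0 | 47.7% / – | 34.8% / – | 4.6% / 4.7% |

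A further repeat gave about 9%, 17–23% and 26–37% at 0.5, 1.0 and 1.5 SD. Together the runs give 8–10%, 16–23% and 26–37%. At 0.25 SD the rate is 5–6%, hardly above nominal.

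**Upper limit.** For a marker identical to BRAF status, the rate is the power of a two-proportion test, Φ[(Δ − 1.96·SE₀)/SE₁].

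- Arm C at 30%: pooled proportion 42.6/88 = 0.484, SE₀ = 0.1094, SE₁ = √(0.24/54 + 0.21/34) = 0.1031. This gives Φ[(0.30 − 0.2144)/0.1031] = Φ(0.83) = 80%.
- Arm C at 35%: SE₀ = 0.1095, SE₁ = 0.1055. This gives Φ[(0.25 − 0.2145)/0.1055] = Φ(0.34) = 63%.

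**Within-arm fitting.** Univariate Wald tests within a single arm gave 3.3% (n = 27) and 3.2–3.4% (n = 34), so there is no inflation.

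**The case against.** The strongest objection is that pooling is inferred. Univariate means one predictor; it does not mean all arms together. The trial is non-comparative, arms A/B and C have separate hypotheses and sample sizes, and the discussion intends to read the wild-type arm in its own right. Univariate models within each arm would fit that design and would not have this problem. The article is also condensed, and an analysis plan that is not shown may settle the matter. This stands as a limit on the claim. It does not remove the point, because the article names a method that leaves out the arm and does not confine it to one arm.

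A second objection is that the analysis is declared exploratory. That is true, and no primary or confirmatory result depends on it. But the article uses the label to justify the lack of multiplicity adjustment. Confounding is a different problem, and the label does not address it.

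Several stronger readings are tempting and are not supported:

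- **That such markers will look predictive, or that confounding would dominate the findings.** The rate stays below 50% even at 2 SD, the shifts are assumptions, and no figure in the article shows how far any listed marker differs by BRAF status.
- **That adjustment for arm would show a marker to be predictive.** An adjusted association with outcome is still not evidence that the marker modifies a treatment effect.
- **That post-baseline markers are related to survival from randomisation without allowing for survival to the sample.** The article gives no time origin for the biomarker models, and no size can be put on this.
- **That the missing multiplicity adjustment is an error.** It is a declared choice for exploratory work, and the marker list is still open, so the number of tests is unknown.

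**Conclusion.** The point holds conditionally. As worded, the plan allows a pooled analysis in which BRAF group confounds the marker–pCR association. The false-positive rate then rises with how strongly the marker tracks BRAF status: negligibly for weak tracking, roughly three- to fivefold at 1 SD (16–23% against 5%), and to 63–80% for a perfect proxy.

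This rests on four assumptions: the models are pooled, the plan's assumed pCR rates are about right, the marker shifts are as chosen, and the test is two-sided. The calculations cover pCR only. Recurrence-free and overall survival could be confounded in the same way, but no rate is claimed for them. The consequence is limited to exploratory findings, so this is an inexpensive improvement that should be made and not a threat to the trial's primary result.

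**What to change.** Replace the univariate specification in section 2.6, or in the analysis plan, with one of two statements:

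1. Biomarker–outcome models include treatment arm, as a covariate in logistic models for pathological response and as a stratum in Cox models for recurrence-free and overall survival.
2. Univariate models are fitted and reported separately within each arm.

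Under either option, describe results as associations with outcome, not as predictive effects.

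The first option costs one degree of freedom per model if BRAF status is used and two if arm is used, plus a line of text and minor programming. Arm also covers the drug differences between A and B. The second option needs no extra term, but each model then rests on 27 or 34 patients and has less power. Sample size, data collection and the primary analysis are unaffected.

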## Discussion

3

Although recent advances in the treatment of metastatic melanoma have improved outcomes and survival, resistance and toxicity continue to be responsible for disease progression and mortality.

Neoadjuvant therapy for regional metastases has an established role in several cancers and is investigational in advanced melanoma (24). It may provide advantages such as improving operability and outcomes and facilitating the identification of biomarkers that can guide further lines of treatment.

Patients with clinical stage III melanoma may especially benefit from neoadjuvant treatment because outcomes of surgery alone are very poor. Two phase 2 open-label trials, one with neoadjuvant dabrafenib and trametinib and one with neoadjuvant talimogene laherparepvec, compared to upfront surgery, in advanced resectable melanoma, obtained meaningful benefit with increased event free survival (21, 28).

Triple therapy in the first line obtained encouraging results in ongoing phase III trials in advanced resectable melanoma. Pembrolizumab + dabrafenib + trametinib improved PFS, duration of response (DOR), and OS compared with placebo + dabrafenib + trametinib (29), and atezolizumab + vemurafenib + cobimetinib prolonged PFS and provided a clinically meaningful benefit in median DOR compared with placebo + vemurafenib + cobimetinib (30) in patients with *BRAF*V600E/K-mutant melanoma. Based on such results, this study will evaluate the neoadjuvant treatment with ICB and targeted therapy followed by adjuvant treatment with atezolizumab (an anti-PD-L1). It is expected a good number of pathological responses and a reduction of relapse incidence as well as a survival increase. This study may also help identify biomarkers and understand response mechanisms, analyzing tissue and blood samples obtained before and after systemic treatment.

This study will explore the concomitant or sequence administration of ICB and BRAF inhibitor/MEK/inhibitor, using an FDA approved triple-drug combination, vemurafenib/cobimetinib/atezolizumab. The data from such study will be comparable with data from the pooled analysis (24) and with the recent NeoTrio study (31). NeoTrio found that concurrent dabrafenib/trametinib/pembrolizumab had higher pCR and pathological response rate compared with dabrafenib/trametinib with sequence pembrolizumab and with pembrolizumab alone, but it had a high toxicity (31). Our study, differently from NeoTrio study, will use the triple combination with vemurafenib/cobimetinib/atezolizumab which gave positive results in the phase III study in patients with metastatic melanoma (18, 30) and is currently approved by FDA. Data from the *BRAF* wild-type arm of our study will also be useful to understand whether MEK inhibitors have immune-stimulating or immune-suppressor effect in advanced melanoma.

Comparison of trials may add useful information for the knowledge of this complex therapeutic strategy. As an example, it is known that the pooled analysis by Menzies et al. (24) of six trials on neoadjuvant therapy showed that not only pCR but also partial responses to neoadjuvant treatment gave a clinical benefit. However, this result is not in agreement with the newer PRADO study (phase II study of personalized response-directed surgery and adjuvant therapy after neoadjuvant ipilimumab and nivolumab in clinical stage III melanoma), which confirmed that patients with major pathologic response to neoadjuvant, without adjuvant therapy, had high relapse-free survival and distant metastasis free survival rates. Nevertheless, it was found that patients with partial pathologic response had worse outcomes, with no benefit for 2-year recurrence rate, and should receive adjuvant treatment (32). Therefore, previous data still need confirmation.

In conclusion, we planned a phase II randomized non-comparative study to evaluate neoadjuvant plus adjuvant combined or sequenced vemurafenib, cobimetinib and atezolizumab in patients with high-risk, resectable *BRAF*-mutated and wild-type melanoma, and we expect to improve outcomes in patients with advanced melanoma, with a better insight on the concerned populations through the pathologic examination of tissue samples.

## Ethics

This clinical study was designed, shall be implemented, and will be reported in accordance with the ICH Harmonized Tripartite Guidelines for Good Clinical Practice, with applicable local regulations (including European Directive 2001/20/EC), and with the ethical principles of the Declaration of Helsinki. This protocol, the Informed Consent Forms, any information to be given to the patient, and relevant supporting data have been approved by the Ethics Committee of the Principal Investigator (National Tumor Institute, “G. Pascale” Foundation, U.O.C. Melanoma, Oncology Immunotherapy, and Novel Therapies, Naples, Italy) and will be reviewed before the study is initiated. The study is registered at eudract.ema.europa.eu/protocol.htm (number 2018-004841-17). The key design elements of this protocol will be posted in the publicly accessible database clinicaltrials.gov: NCT04722575. Patient recruitment will be performed at Istituto Nazionale dei Tumori, Fondazione “G. Pascale”, Naples, Italy.

## Data availability statement

The original contributions presented in the study are included in the article/supplementary material. Further inquiries can be directed to the corresponding author.

## Ethics statement

The studies involving human participants were reviewed and approved by Institutional Review Boards of Istituto Nazionale Tumori IRCCS–Fondazione “G Pascale”. The patients/participants provided their written informed consent to participate in this study.
